**Figure 1 F1:**
[figure not shown]
**Flow Diagram of Study Design**.

### Statistical analysis

The primary aim of the statistical analysis is to compare the two arms, with respect to the primary and secondary outcomes, i.e. the time to virological treatment failure and adherence. In both cases, we plan to estimate the deviation between the two arms and assess statistical significance, i.e. the probability that the deviation is due to random variation. The estimation results will be given as point estimates and confidence intervals.

Given the primary end point, the conventional approach for the analysis of risks would be to study the risk ratio and hazard ratio (RR, HR). In addition, the study of the risk difference (RD) will provide information on the expected number of cases that actually benefit from the intervention in terms of avoided failures.

The risk analysis will be carried out using survival analysis techniques. Survival curves will be constructed using the Kaplan-Meier life table technique; these will then be compared using log- rank tests, possibly stratified. Cox regression models will also be employed. As the risks of treatment failure are likely to be rather small, a simplified analysis, using for e.g. Poisson regression will give very similar results. The observed time for any patient will be adjusted for periods that could not be observed due to no-show. Patients withdrawn for reasons other than virological failure, and patients lost to follow-up, will be right censored, but included in the analysis for the periods during which they could be observed.

With regard to the secondary outcome, the different adherence variables will be numeric hence other models and tests are required. The main aims are to study the average adherence, variation of adherence within as well as between participants, and trends over time. Increased adherence might be of limited value if the variation remains large. Different models for Analysis of Variance (ANOVA) with provision for repeated measurements will be used. The distribution of adherence at any point in time is likely to be negatively skewed. This will necessitate analysis, using distribution-free (non-parametric) statistical methods, or transformations of original data.

Intention to treat analyses (ITT) will be used for the comparison of primary and secondary outcomes between arms. Thus a patient assigned to the intervention arm will be considered as belonging to that arm even if he or she clearly does not perform according to the protocol.

Analyses will be carried out using the program STATA, version 10.

#### Interim analysis

An independent data safety and monitoring committee, including a statistician, has been established to perform an interim analysis. This analysis of the failures occurring in each arm is scheduled to occur when 150 patients have been recruited into each arm. The interim analysis team will carry out the analysis blinded. The primary aim of the interim analysis is to assess if the intervention arm shows a clearly better, or worse, outcome, in terms of failures, than the control arm. The result will guide the discussion about whether to continue or end the trial. The interim analysis will also consider the accumulated reported adverse effects in both two arms.

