### Outcome Measures

#### Primary outcome

The primary outcome will be measured as time (in weeks) to virological failure which defined as a plasma viral load of more than 400 copies/ml on each of two consecutive samples measured one month apart, six months after initiating ART. The date of the first assessment of a plasma viral load more than 400 copies/ml will be documented as the date of virological failure. Virological failure was chosen as a primary outcome, as this is a biological surrogate marker of poor adherence, and is an objective measure. For the primary outcome, patients in each arm will be followed up for 24 months (after initiating ART) or until virological failure occurs, whichever is earlier.

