### Sample size

The primary end point in the trial will be time to virological failure as estimated using the standard life-table technique and illustrated by Kaplan Meier survival curves [26]. The baseline assumptions in the sample size calculation, are that the risk for virological failure in the control arm will be 10% [27] (risk rate 0.1), while the intervention will reduce this risk to 3% (0.03). The assumptions for this level of risk in the control arm and intervention arm are based on a review of available literature [8,28,29]. Stata 10 sample size software module was used to determine the necessary sample size for a comparison of the survival times between the two arms, using the log rank two-sided test. The significance level or alpha level was set to 0.05 for a two-tailed test, and the power (probability to detect a deviation of hazard ratio from unity) requested was 0.90 (90%). Given this, a sample size of 266 in each arm (n = 1:1) was determined. Assuming an attrition rate of 10%, this sample size was inflated by 10% to compensate for loss to follow-up, which gives a total sample of 292 in each arm. Thus a total of 600 patients newly initiated on ART will be recruited, with 300 in each arm of the trial. By having 300 participants in each arm, the trial will have sufficient power to detect a clinically significant difference between the arms. With a planned recruitment rate of 4-8 participants per week at each centre, the recruitments for the study will be completed within approximately 12 to18 months.

A flow diagram of the study design is presented in figure 1.

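### The only interim comparison of virological failures is triggered by recruitment, at a point when about 0 to 1 confirmed failures are expected against about 35 needed, so it cannot meet its stated primary aim

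*Protocol article*

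**What the plan says.** Three sections of the protocol article bear on this point.

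- **Interim analysis.** The trigger is a recruitment count: "This analysis of the failures occurring in each arm is scheduled to occur when 150 patients have been recruited into each arm". The primary aim is to "assess if the intervention arm shows a clearly better, or worse, outcome, in terms of failures, than the control arm". On its use: "The result will guide the discussion about whether to continue or end the trial". Accumulated adverse effects are reviewed at the same look. No minimum follow-up or number of failures is attached to the trigger, and no later look is described.
- **Primary outcome.** Failure is "a plasma viral load of more than 400 copies/ml on each of two consecutive samples measured one month apart, six months after initiating ART", and "patients in each arm will be followed up for 24 months (after initiating ART) or until virological failure occurs, whichever is earlier".
- **Sample size.** The assumed failure risks are 10% (control) and 3% (intervention), tested with a two-sided log-rank test at 0.05 with 90% power, giving 266 per arm. Accrual is stated as follows: "With a planned recruitment rate of 4-8 participants per week at each centre". Completion is expected in about 12 to 18 months for 600 patients.

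**The concern.** The look compares failures, but it is timed by enrolment. A failure cannot be dated before about six months of treatment or confirmed before about seven. If the first 300 patients are enrolled in roughly that time, the committee is asked for a view on continuing or ending the trial when hardly any outcome can have occurred. The trial would then have no working interim assessment of its primary endpoint, because this is the only look described.

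**Working it through.** **1. Reproducing the plan's own figure.** Freedman's log-rank formula, with the stated 10%, 3%, two-sided 0.05 and 90% power:

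- HR = ln(0.97)/ln(0.90) = 0.289
- Events = (1.960 + 1.282)² × [(1 + 0.289)/(1 − 0.289)]² = 10.51 × 3.288 = 34.5, so about 35
- N = 34.5/0.065 = 531.5, or 266 per arm, where 0.065 is the mean of 10% and 3%

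This matches the protocol exactly, so about 35 failures is the information on which the design rests. With 300 per arm and no attrition, 300 × 0.10 + 300 × 0.03 = 39 would be expected.

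**2. Earliest countable failure.** Month 6 is about week 26. One month (4.3 weeks) for the second sample gives about week 30.3.

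**3. Calendar time of the 300th patient.** Two centres at 4 to 8 per week give 8 to 16 per week in total. The 12 to 18 months stated for 600 imply about half that time for 300.

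**4. Patients who could have a confirmed failure by then.** Accrual is taken as uniform and treatment as starting at recruitment (assumptions). The count is (week of trigger − 30.3) × weekly rate, or 0 if negative.

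| Pace | Week of 300th patient | Past month 6 | Past month 7 |
|---|---|---|---|
| 16/week | 300/16 = 18.8 | 0 | 0 |
| 600 in 12 months | about 26 | about 1 | 0 |
| 8/week | 300/8 = 37.5 | 92 | 57 |
| 600 in 18 months | about 39 | about 100 | 67 |

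**5. Expected confirmed failures, both arms together.** The 10% and 3% are taken as 24-month risks (assumption).

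- The two faster paces give 0.
- For the two slower paces, constant hazard from treatment start gives 1.1 and 1.3. Constant hazard from month 6 gives 0.2 and 0.3.
- In the extreme case, where every 24-month failure is already present at month 6, the results are 57 × 0.065 = 3.7 and 67 × 0.065 = 4.4.

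Against 35 events this is 0 to about 4% under constant hazard (1.3/35) and at most about 12% in the extreme case (4.4/35).

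**6. What such counts can show.** If all d failures fall in one arm, the two-sided exact p is 2 × 0.5^d. This gives 1.0 for one failure, 0.50 for two and 0.125 for four. At least six failures, all in one arm, are needed to fall below 0.05 (p = 0.031).

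**7. Sensitivity.** Counting first raised samples without confirmation, at the slower paces, gives about 0.5 to 2.1 failures under constant hazard and 6.0 to 6.5 in the extreme case. The conclusion does not turn on the confirmatory month.

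**The case against.** The other side has several good points.

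- **Harm.** A reader might infer that the look offers no protection against harm. It does offer some: the adverse-effect review does not depend on the failure definition and is workable at 150 per arm. The criticism is confined to virological failures.
- **Patients in a position to fail.** At the slow end, 57 to 67 of 300 (19% to 22%) are past month 7, so it would be wrong to say that nobody can be assessed. What is scarce is expected failures. The 16-per-week pace would also fill the trial in 600/16 = 37.5 weeks, faster than the stated 12 to 18 months. But the 12-month pace gives zero as well.
- **Type I error.** The protocol says of the sample size: "The significance level or alpha level was set to 0.05 for a two-tailed test". A reader might infer that the interim look inflates this. Two looks at 0.05, one of them at half the information, would give 8.3%, but the plan states no interim test at 0.05 and no look at half information. A boundary may sit in an unseen analysis plan or committee charter. At the planned timing there is almost no alpha to spend.
- **Wrong stop.** A reader might also infer that a chance split could end the trial. This is speculative: the aim demands a clear difference, an independent committee with a statistician judges it, and even a 4–0 split gives p = 0.125.
- **Unseen documents.** An unseen boundary does not answer the core point. The trigger is fixed in this protocol, and no boundary makes 0 to 4 events informative.
- **Time frame of the risks.** The protocol does not attach a time frame to the 10% and 3%. Reading them as 24-month risks is an inference from the follow-up period.

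**Conclusion.** The concern holds for the failure comparison. On the protocol's own failure definition, accrual and risks, the interim look would hold about 0 to 1 expected confirmed failures, and about 4 in the extreme case, out of about 35. It cannot show a clearly better or worse outcome on failures, which is its stated primary aim.

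The result rests on uniform accrual, treatment starting at recruitment, 24-month risks and no attrition. A gap between recruitment and treatment start, or attrition, would lower the counts further. Recruitment at half the slowest planned rate (4 per week in total, outside the plan) would still give only about 3 to 6 confirmed failures under constant hazard.

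The final log-rank test, the sample size and the primary estimate are not affected. The expected consequence is a look without information, followed by a trial that continues. This is something that should be fixed, not a fatal flaw.

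**What to change.** Separate the two purposes of the look. Keep the adverse-effect review at 150 per arm. Trigger the comparison of failures by a number of confirmed failures, for example about 17 (half of 35). State a strict two-sided limit covering both better and worse, such as Haybittle-Peto p<0.001. With that limit at half the information and 1.96 at the end, the overall two-sided type I error is 0.0502 (bivariate normal calculation), so the final test can stay at 0.05 and the sample size is unchanged.

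The cost is a one-paragraph amendment to the protocol and the committee charter, with no extra patients. There are two drawbacks to accept knowingly.

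- **Late timing.** At 16 to 8 patients per week, with constant hazard from treatment start or from month 6, the 17th confirmed failure is expected at about months 16 to 23. Recruitment at those rates ends at about months 9 to 17 (37.5 to 75 weeks), so stopping would save follow-up, not enrolment.
- **Low chance of crossing for benefit.** With 17 failures an exact test needs a 16–1 split or better (p = 0.0003; a 15–2 split gives 0.0023). Under the design HR a failure falls in the intervention arm with probability 0.289/1.289 = 0.224, so the chance of at most one in 17 is about 8% (about 23% by normal approximation).

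If the sponsor does not want a late look, the minimum change is to state that the look at 150 per arm serves the adverse-effect review only, and to remove the comparison of failures from its aims.

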#### Subgroup analyses

In addition to analyses that aim at hypothesis testing, we will also carry out exploratory analyses that will produce descriptive data that can be used for subsequent hypothesis generation and to provide additional information about the effects of the intervention on different participant sub groups (by age, sex, rural/urban, socioeconomic strata, literacy).

### Other sub-studies

The trial will also provide a clinical platform to study adverse drug reactions to national first-line ART among newly ART-initiated individuals. Other clinical studies will include those on the incidence of opportunistic infections, on immune reconstitution inflammatory syndromes, and on the influence of ART on changes in nutritional status and dietary intake, within two years of initiating ART. In addition, in the intervention arm, adherence reported over the telephone will be compared with self reported measures. Qualitative studies exploring the responses and perceptions of intervention arm participants towards the mobile phone intervention and the experiences of clinic staff with this modality will be included.

### Economic analysis

A cost-effectiveness analysis of the intervention from a governmental perspective will be performed. The principle of marginal costing will be used to cost the resources utilised in the alternative strategies. Full costing, by absorption costing or by activity based costing, would not be relevant for this study, since the purpose is to provide a basis for rational decision making. In a decision-making process the fixed costs are irrelevant, since they will not be affected by the choice of either alternative strategy. All costs of a historical nature, so-called sunk costs such as resources invested in buildings, equipment, and vehicles will be ignored. Only costs related to the future, from the onset of the study, will be recorded.

A further restriction is that only differential costs will be collected, i.e. costs that are different between the two alternative strategies. Costs that are common to the two alternative strategies will be ignored. In the case of use of materials, the replacement cost will be used, i.e. not the accounting cost or the historical cost of the resources, but the current cost of replacing the resources will be applied.

The process of costing will be as follows. First, the relevant resources will be identified that are differential for the alternative strategies. Second, the quantities of resource use will be measured, e g the time spent by different clinic staff on the patient. Third, the cost of the resource consumption will be calculated, by multiplying the time or numbers of the resource with a standard cost of the resource. The historical prices recorded in the accounts will not be used, since these would result in measuring differences in price levels rather than differences in resource consumption.

### Ethical issues

The study protocol has been ethically approved by institutional ethical review boards in all the participating and collaborating institutions. The rights and welfare of the participants will be protected according to the Declaration of Helsinki Ethical Principles for Medical Research Involving Human Subjects. Clinical care and emergency medical services are provided by the participating institutions. Data that is collected as part of the study will be not be linked to any individual, personal identifiers will not be used in data storage, and confidentiality will be maintained at all levels of data management.

An important consideration in this study design is the possibility of stigma, as patients may not have disclosed their HIV status to people they live and work with. It is conceivable that some stigma may be attached to receiving a mobile phone from the hospital. Participants in the intervention arm also run the risk of being stigmatized, due to the receipt of regular text and voice messages. To minimize this risk, the picture messages that the patients will receive as reminders, will be neutral pictures, which the patient is shown, and approves at the enrollment visit. With regard to the automated call, the patient chooses a particular time based on his schedule, when s/he has the privacy to receive and respond to the call. Detailed counseling on potential stigma issues will accompany routine counseling at recruitment and at subsequent study visits.

## Discussion

### Methodological

As patients are not blinded to the intervention they receive, a Hawthorne effect in the intervention arm is a possibility. This could exaggerate the difference in adherence between the two arms. Also the attention given to trial participants at the clinics, in itself may raise adherence in both arms.

With regard to the intervention, the receipt of automated calls can be recorded, hence the study team will know that the call was received and attended to (based on the response received from the patient). However, though patients will be trained to look at the sms on their phone, it is not possible to know if the patient actually read the sms sent out, or if it remained unread on his/her phone. Interactive sms alone was not chosen as a method in this study, given the low usage of the sms function in this setting [23].

The trial will study the influence of the entire intervention. It will not be able to assess the degree to which each component of the intervention contributed to any observable difference.

### Telecommunications in healthcare in resource limited settings

The World Health Organization has indicated that incorporating the use of newer technology, such as telecommunications, in resource-limited settings to enhance healthcare delivery, is a priority [30]. Mobile phones offer promise for use in healthcare, particularly in low income settings, given the centrality of their use in everyday life. Living in resource-poor environments is not a barrier to the use of mobile phones. There is evidence that the existence of a so-called "digital divide" along the socio-economic gradient is less pronounced when it comes to mobile phones than with regard to other communication technologies, such as the Internet [14].

The telecommunications network in India is the third largest in the world, with a total of 509 million connections, of which 471 million are mobile telephone connections [31]. The use of mobile phones in the country has increased rapidly along with falling costs of mobile telephone services. India has also begun to scale up of it's National AIDS control program, providing first-line ART free of cost. In a pilot study at one of the trial centers clinic [23], we found that 75% of clinic attendees owned mobile phones, making this a contextually appropriate intervention.

Though studies on the use of telephones in promoting adherence to ART exist [28,32], they have been carried in high-income areas of the world, where fixed telephone infrastructure exists. These trials reported no influence on time to virological failure, but did indicate a positive impact on self-reported adherence.

Mobile telephones are increasingly relevant in India, and in many parts of the developing world, as they are low-cost, easily available and used commonly in everyday life [33]. The results of this trial are expected to provide evidence of the influence of mobile phone reminders on improving adherence to first-line ART in an Indian context. This intervention is also expected to delay treatment failure, and hence preserve expensive second-line ART. As this is the first such trial in India as well as in Asia, the results will highlight key implications for other low-income settings globally, where there is rapid growth in acess to mobile phones, and the potential for their incorporation into many aspects of routine healthcare.
